Currently, reduction of IOP remains the focus of all therapeutic approaches for the majority of glaucoma patients, including those with NVG. For NVG, however, IOP-lowering medications are moderately helpful because outflow is obstructed and the accompanying inflammation and proliferative stimulus lead to the very poor success rate of fistulating glaucoma surgery. Currently, the common therapy for neovascularisation is pan-retinal photocoagulation (PRP), although additional anti-VEGF intravitreal injections have become more and more common for the therapy of neovascularisation. Thermic laser coagulation of the retina by PRP is strongly advocated and practiced widely for the management of iCRVO if new vessels have already formed [10, 11]. However, no definite guidelines exist regarding the exact indication and timing of PRP. As an alternative method of selective retinal ablation, pan-retinal cryotherapy may be performed on the peripheral fundus if the ocular media are too hazy for laser application.

There is a clear need to widen the existing therapeutic options for the treatment of iCRVO to prevent neovascularisation and NVG, with a specific focus on noninvasive therapeutic options aimed at prevention or early management respectively of the neovascular component of iCRVO. Hence, it is expected that aganirsen will benefit patients with iCRVO by interfering at an early stage in the neovascularisation process. Understanding the natural course of NVG, including biomarker and risk factor analysis, will further support the evaluation of new diagnostic and therapeutic interventions. These results could help to make early NVG diagnosis independently of an increased IOP by analysis of body fluids.

The primary objective of this multicentre randomised controlled study is to assess the efficacy and safety of aganirsen relative to placebo in preventing NVG in patients with iCRVO. We will evaluate the appearance of neovascularisation and the rise in IOP after 24 weeks (co-primary endpoint). We hypothesise that each of the two tested aganirsen doses will be superior to the placebo in preventing NVG at week 24. This study will also evaluate the effective dose of aganirsen.

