The secondary objectives are to evaluate the efficacy of two aganirsen doses, to assess the aganirsen efficacy relative to placebo on time to, and intensity of, additional interventions, such as PRP or cryotherapy, to compare the effect of aganirsen and placebo on health outcome and quality of life (QoL) and to confirm a positive safety profile of aganirsen.

The aim of the imaging substudy is to develop an objective quantification of neovascularisation in the anterior part of the eye. For the biomarker substudy, the aim is to find possible biomarkers for iCRVO and NVG in tears and serum. The aim of the risk factor substudy is to identify potential novel risk factors for iCRVO and to evaluate if some of those parameters can be useful to differentiate patients who are at a higher risk of developing NVG.

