Additional exclusion criteria were defined for the eligibility of patients for the risk factor substudy: age 65 years or older, renal insufficiency and acute malignant or inflammatory reaction (systemic or local).

The co-primary efficacy endpoints combine a neovascularisation component: presence of anterior segment neovascularisation (NVI or NVA), NVD and/or NVE in the study eye requiring PRP rescue treatment or cryotherapy rescue treatment up to week 24 scored dichotomously (yes/no) and an IOP component: percentage change (≥20%) in IOP compared to baseline and >21 mmHg in the study eye scored ‘failure’, while otherwise ‘success’.

The secondary endpoints of the trial are the time of development of secondary NVG in the study eye up to week 24 (in case aganirsen does not totally inhibit but slows down the development of NVG); the time of development of anterior segment neovascularisation (NVI or NVA); NVD or NVE in the study eye requiring PRP or cryotherapy up to week 24; the development of changes in BCVA (ETDRS letter score) in the study eye up to week 24 (from baseline); the development of needed additional laser treatments and re-treatments in the study eye at up to week 24 including the intensity of the needed additional treatment; the development of changes in the size of retinal nonperfusion areas in the study eye up to week 24 in comparison with the baseline; the development of changes in the National Eye Institute Visual Function questionnaire 25 (NEI-VFQ-25) health questionnaire total score at week 24 in comparison with the baseline; the development of changes in the EuroQoL five dimensions questionnaire (EQ-5D) health questionnaire (validated questionnaires) score at week 24 in comparison with baseline; absolute change from baseline in central retinal thickness in the study eye, assessed by spectral domain optical coherence tomography (SD-OCT) at week 24; NVG classification at 24 weeks on a scale from 1 (non-NVG) to 6 (most advanced NVG) based on central reading of neovascularisation and incidence, causality and intensity of adverse events between the treatment arms.

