All randomised subjects, regardless of treatment group, may receive rescue treatment (e.g. PRP, cryotherapy or other, as routinely performed at the clinical site) at any time during the trial if they progress to anterior segment neovascularisation (NVI or NVA), NVD, or clinically relevant NVE in the fundus. In this case, the primary endpoint is reached and the patient will not further receive study medication. Should a patient receive rescue treatment with intravitreal anti-VEGF (i.e. Lucentis®, Eylea®) because of macular oedema (individual decision of the investigator), the patient will not further receive the study drug, but will be followed up for safety reasons.

The clinical trial will be performed in consideration of the Declaration of Helsinki and the International Conference on Harmonisation – Good Clinical Practice (ICH-GCP). The protocol (Version No.:1.4/Date 7 Jan 2015 Final) is approved by the institutional Ethics Committee from the Landesärztekammer Rheinland-Pfalz, Germany, and by the French Ethics Committee. Ethics approval in other participating countries/sites will follow. Any protocol amendment will be approved by the Ethics Committees and will be distributed to all participating trial sites via the sponsor’s delegated clinical research organisation. Additionally, all necessary documents in the current version will be available on a password-protected website. Personal information of participants will be treated as confidential. Only anonymous data will be forwarded to the sponsor for scientific evaluation. Data entry and storage is performed via an electronic data capture (EDC) system, including plausibility checks.

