### Secondary efficacy analysis

Aganirsen arms combined versus placebo: secondary analyses will be considered exploratory. Time to development of anterior neovascularisation will be compared by *t* test or Wilcoxon rank sum test (depending on distribution), since missing data will be imputed using LOCF and there will be no censored data.

Continuous change from baseline to week 24 parameters (e.g. size of retinal nonperfusion areas) will be assessed by analysis of covariance (ANCOVA), the covariate being a subject’s baseline variable, to prevent regression towards the mean. If the model shows a lack of fit, ANCOVA will be conducted on ranked data. The number of additional laser treatments will be compared between groups by Poisson regression.

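### The objective covers the intensity of all additional interventions, cryotherapy included, but the only stated analysis counts laser treatments, so an eye rescued without laser scores zero

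*Protocol article*

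**What the plan says.** Five places in the protocol article bear on this.

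- **Objective** (Background, secondary objectives): "to assess the aganirsen efficacy relative to placebo on time to, and intensity of, additional interventions, such as PRP or cryotherapy".
- **Endpoint** (list of secondary endpoints, printed under Exclusion criteria): "needed additional laser treatments and re-treatments in the study eye at up to week 24 including the intensity of the needed additional treatment". The first half names laser; the closing clause on intensity is not tied to laser.
- **Analysis** (Secondary efficacy analysis): "The number of additional laser treatments will be compared between groups by Poisson regression". No other analysis of rescue intensity is stated.
- **Permitted rescue** (rescue paragraph, also under Exclusion criteria): subjects "may receive rescue treatment (e.g. PRP, cryotherapy or other, as routinely performed at the clinical site) at any time during the trial", on progression to neovascularisation. Intravitreal anti-VEGF is named separately as rescue for macular oedema.
- **When cryotherapy replaces laser** (Background): "pan-retinal cryotherapy may be performed on the peripheral fundus if the ocular media are too hazy for laser application".

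The sections Co-primary efficacy I and II count any rescue treatment as an event or failure, whatever the modality.

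**The concern.** The variable to be counted is narrower than the objective it serves and narrower than the rescue the trial allows. An eye with new vessels that is treated by cryotherapy alone has had an additional intervention of exactly the kind the objective names, yet its laser count is 0. The same applies to an eye rescued only by another non-laser method under the open category in the rescue paragraph.

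These eyes are then indistinguishable from eyes that needed nothing. No change of count model repairs this, because the fault is in what is counted. The eyes concerned may also not be a random subset, since the article itself links cryotherapy to media too hazy for laser. At stake is one exploratory comparison: it could lose events, and it could be distorted in either direction if non-laser rescue were commoner in one arm.

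**Working it through.** The article gives no figure for this analysis, so there is none to reproduce. The check has two parts.

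**1. How one eye is scored.** Take an eye that develops new vessels and is rescued with cryotherapy only.

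| Place in the article | Result for this eye |
|---|---|
| Co-primary efficacy I (NVG) | Yes (event) |
| Co-primary efficacy II (IOP) | Failure, through the rescue clause |
| Secondary objective, intensity of interventions | One or more interventions |
| Poisson regression of laser treatments | Count 0 |

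The zero is inferred from the variable named; the article does not state it. It arises only in eyes that receive no laser at all.

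**2. How many eyes, and what happens to the ratio.**

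Inputs from Statistics: 200 aganirsen and 100 placebo evaluable subjects; planning NVG rates 0.25 and 0.48.

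Assumptions: the rescue rate equals the planning NVG rate; each rescued eye has one session; a share s of rescued eyes receives no laser. The article does not give s, so a range is shown.

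Expected rescued eyes: 200 × 0.25 = 50 and 100 × 0.48 = 48, together 98. True zeros: 150 and 52.

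False zeros = rescued eyes × s. Their share of all zeros = false zeros / (true zeros + false zeros). With s equal in both arms:

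| s | False zeros, placebo | False zeros, aganirsen | Total of 98 | Share of placebo zeros | Share of aganirsen zeros |
|---|---|---|---|---|---|
| 10% | 4.8 | 5 | 9.8 | 4.8/56.8 = 8.5% | 5/155 = 3.2% |
| 20% | 9.6 | 10 | 19.6 | 9.6/61.6 = 15.6% | 10/160 = 6.25% |
| 30% | 14.4 | 15 | 29.4 | 14.4/66.4 = 21.7% | 15/165 = 9.1% |
| 50% | 24 | 25 | 49 | 24/76 = 31.6% | 25/175 = 14.3% |

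Laser-only ratio, aganirsen to placebo = 0.25 × (1 − s_A) / [0.48 × (1 − s_P)].

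- Equal shares: the factors cancel, 0.25/0.48 = 0.52, the ratio for all rescue.
- s_A = 10%, s_P = 30%: 0.225/0.336 = 0.67, benefit understated.
- s_A = 30%, s_P = 10%: 0.175/0.432 = 0.41, benefit overstated.

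So equal shares cost events but leave the ratio unbiased. Only a difference in shares between the arms moves it.

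**The case against.** Several arguments on the other side are sound.

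- **The endpoint is not plainly laser-only.** Its closing clause on the intensity of the needed treatment is general and echoes the objective, and the detailed scoring may sit in a full protocol or SAP. This stands as a description of the endpoint. It does not remove the point, because the article fixes a specific variable for the analysis, and a SAP that followed it would carry the mismatch forward.
- **Non-laser rescue is captured elsewhere.** Both co-primary analyses count it, and the secondary endpoint on time to neovascularisation names cryotherapy. This stands and limits the harm to one exploratory count.
- **Site habits should not favour an arm.** A reader might infer that differing practice across about 35 sites biases the comparison. Randomisation is blocked within site, and investigators and site staff are masked, so local preference should be balanced. Only a difference between the arms in the condition of the rescued eyes would plausibly make the shares differ, and the article offers no evidence of one.
- **Anti-VEGF is a weak example.** A reader might count every eye given an injection as a false zero. The anti-VEGF rescue the article names is for macular oedema, which is not rescue for neovascularisation. For neovascularisation, the Background describes injections as additional to PRP, and an eye that has both has a laser count of at least 1. Injection-only rescue for neovascularisation is possible under the open category, but its frequency is unknown.
- **Eligibility limits hazy media.** Eyes without fundus photographs or angiograms of sufficient quality are excluded, so mainly haze that develops after entry matters. This may make the non-laser share small; it does not make it zero.
- **Adding modalities has its own problem.** A total over PRP, cryotherapy and other sessions depends on how many sessions each modality needs. This stands and is why the split must be reported.

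**Conclusion.** The mismatch is real and rests on the article's own text: the objective names cryotherapy, the rescue paragraph permits it, and the stated analysis does not count it. Cryotherapy-only rescue is the firm case.

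The size is unknown. About 10 to 49 of 98 expected rescued eyes would be false zeros, but only under assumed non-laser shares of 10% to 50% and with the planning NVG rates taken as rescue rates. The range 0.41 to 0.67 around 0.52 illustrates unequal shares; it does not predict bias, and the documents support no particular direction. Nor do they support a reading in which the primary result is affected: all rescue counts there, and the secondary analyses are declared exploratory without Type I error control. This is a minor-to-moderate point, worth correcting because the wording as it stands misclassifies rescued eyes against the trial's own objective.

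**What to change.** In the list of secondary endpoints and in Secondary efficacy analysis, replace the count of laser treatments with the number of rescue treatment sessions of any modality (PRP, cryotherapy or other) given for neovascularisation in the study eye up to week 24. Report the split by modality and arm, and keep the laser-only count as a supportive analysis.

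Two limits keep the endpoint within the present objective. Do not add treatment for raised pressure, which is not a trigger in the rescue paragraph. Report anti-VEGF given for macular oedema separately.

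The cost is the wording of one secondary endpoint and its analysis, settled before unmasking. Table 1 already records concomitant medications and procedures at every visit, so no new visit is needed; the indication for each procedure must be identifiable in those records. The small downside is that sessions of different modalities are added together, so the total should not be read without the split. No clinical rule changes.

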### Statistics

Presentation of the sample size is based on both aganirsen doses combined demonstrating superiority placebo on the co-primary endpoints of neovascularisation and IOP at 24 weeks. Calculation of the sample size is based on the following: (1) An aganirsen to placebo ratio of 2:1, (2) Neovascularisation measured dichotomously (NVG = yes/NVG = no) with estimated disease rates in the population of 0.25 for aganirsen and 0.48 for placebo. Testing of neovascularisation will be done using the normal approximation to the chi-square distribution for consistency with O’Brien-Fleming Alpha spending, which is also computed based on normal approximation, (3) IOP measured dichotomously with estimated rates of events in the population of 0.24 for aganirsen and 0.41 for placebo at 24 weeks and (4) Up to four performed analyses. Based on albeit heterogeneous historical data, we estimate that 25% of subjects in the aganirsen group and 48% in the placebo group will develop NVG by 24 weeks. Given a 2:1 aganirsen to placebo assignment ratio, a total of 300 evaluable subjects – 200 with aganirsen and 100 with placebo – will provide 80% power to reject the null hypothesis that aganirsen is no better than placebo. Power computation is based on the chi-square test with a two-sided alpha = 0.05. Assuming that approximately 10% of subjects will not be evaluable due to loss to follow-up and other reasons, a total of 333 subjects are planned for this trial. Missing values of NVG and IOP will be imputed using the last observation carried forward (LOCF) method.

Primary efficacy will be assessed up to four times: two initial futility analyses, followed by an interim analysis for success/futility/continuation and a final analysis. The data will be summarised in tables listing the mean, standard deviation, minimum, median, maximum and number of subjects in a group for continuous data or in tables listing count and percentage for categorical data, where appropriate. Data listing by subject will be provided. The effects of noncompliance, dropouts and covariates, and their interactions with treatment will be assessed to determine the impact on the general applicability of results from this study. Secondary comparisons will be considered exploratory, so that there will be no Type I error adjustment for multiple secondary comparisons.

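### Poisson regression of the laser-treatment count does not assure correct standard errors, because laser follows only after neovascularisation and re-treatments are counted; robust variance would cover this (minor, exploratory analysis)

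*Protocol article*

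**What the plan says.** The model is fixed in the protocol article, Secondary efficacy analysis: "The number of additional laser treatments will be compared between groups by Poisson regression". The groups are the combined aganirsen arms and placebo.

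The endpoint is in the list of secondary endpoints, which follows the exclusion criteria: "the development of needed additional laser treatments and re-treatments in the study eye at up to week 24". The same item adds the intensity of the additional treatment. The rescue paragraph after that list allows PRP, cryotherapy or another local routine treatment once neovascularisation appears.

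The Statistics section plans on "estimated disease rates in the population of 0.25 for aganirsen and 0.48 for placebo" for the neovascularisation endpoint, with "a total of 300 evaluable subjects – 200 with aganirsen and 100 with placebo". The article gives no expected number of laser sessions per treated eye. Secondary comparisons are declared exploratory.

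**The concern.** Poisson regression takes its standard errors from the assumption that variance equals mean. The design describes something else: a yes/no gate (does the eye convert?) followed by a number of sessions in the eyes that pass it. Repeat sessions in the same eye push the variance above the mean. A gate followed by a single session pulls it below.

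The rate ratio itself is not in question, since in a two-group comparison it is the ratio of the arm means. Its confidence interval and p-value are. The article's stated secondary objectives include the intensity of additional interventions, so this interval is likely to be read as evidence on treatment burden even though it is exploratory.

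**Working it through.** **No stated figure to reproduce.** The article gives no number for this analysis. The rates and group sizes borrowed from the sample-size paragraph fit its power statement: at two-sided alpha 0.05 with 200 v 100, power is 97.7% for neovascularisation (0.25 v 0.48) and 85.2% for IOP (0.24 v 0.41). The product, if independent, is 83.3%, against a stated 80%. This shows only that the inputs are coherent; it does not bear on the count model.

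**Inputs.**
- p, the share of eyes with any laser: 0.25 (aganirsen) and 0.48 (placebo), used as a proxy. Overall (200 × 0.25 + 100 × 0.48)/300 = 98/300 = 0.327, so about 67% zeros overall, 75% on aganirsen and 52% on placebo.
- m and v, the mean and variance of sessions in a treated eye: not in the article, so assumed.

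**Formula.** Let the count be B × S, with B = 1 with probability p and S the sessions in a treated eye. The mean is pm and the variance is p(v + m²) − p²m², so

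variance/mean = (v + m²)/m − pm.

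At p = 0.327:
- one session each (m = 1, v = 0): 1 − 0.327 = 0.67
- 1 + Poisson(0.2) (m = 1.2, v = 0.2): 1.64/1.2 − 0.392 = 0.97
- 1 + Poisson(1) (m = 2, v = 1): 5/2 − 0.653 = 1.85
- 1 + Poisson(2) (m = 3, v = 2): 11/3 − 0.980 = 2.69

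**Type I error.** Writing φ for variance/mean, a nominal 5% Poisson test rejects with probability of about 2 × (1 − Φ(1.96/√φ)). For φ = 0.67, 1.85 and 2.69 this gives about 1.7%, 15% and 23%.

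**Simulation.** There were 40,000 trials per scenario, 200 v 100, with no treatment effect and the same p in both arms. Entries are for p = 0.25 / 0.327 / 0.48.

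| Sessions per treated eye (assumed) | Variance/mean | Poisson type I error, % | Robust SE ÷ Poisson SE |
|---|---|---|---|
| always 1 | 0.75 / 0.67 / 0.52 | 2.3 / 1.7 / 0.7 | 0.87 / 0.83 / 0.73 |
| 1 + Poisson(0.2), mean 1.2 | 1.07 / 0.97 / 0.79 | 5.6 / 4.5 / 2.8 | 1.03 / 0.99 / 0.89 |
| 1 + Poisson(0.5), mean 1.5 | 1.46 / 1.34 / 1.11 | 10.3 / 8.8 / 6.5 | 1.20 / 1.16 / 1.05 |
| always 2 | 1.50 / 1.35 / 1.04 | 10.7 / 8.9 / 5.5 | 1.23 / 1.17 / 1.03 |
| 1 + Poisson(1), mean 2 | 2.00 / 1.85 / 1.54 | 16.2 / 14.9 / 11.6 | 1.41 / 1.36 / 1.24 |
| always 3 | 2.25 / 2.02 / 1.56 | 19.5 / 16.5 / 11.6 | 1.51 / 1.43 / 1.26 |
| 1 + Poisson(2), mean 3 | 2.92 / 2.69 / 2.23 | 24.9 / 23.1 / 18.8 | 1.71 / 1.64 / 1.49 |
| 1 + Poisson(3), mean 4 | 3.75 / 3.44 / 2.83 | 31.4 / 29.3 / 24.7 | 1.94 / 1.86 / 1.68 |

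The robust-variance test rejected in 4.5% to 5.2% of trials in every cell.

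**The case against.** The strongest defence is that the article devotes one sentence to this model and names only its family. It does not rule out a scale parameter or robust variance, and such details usually sit in the full protocol or SAP, which are not shown. That stands to this extent: the article's silence on dispersion is not in itself an error, and the full documents may already deal with it. But the model is a stated choice, and its default standard errors do not suit the count described. The same section provides for poor fit in its neighbours (a rank test for the time endpoint, ranked data for ANCOVA) and has no such sentence for the count.

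A reader might infer more than the documents support:
- **That the standard errors will be wrong.** This does not follow. Near 1.2 sessions per treated eye, or with exactly two at the placebo rate, they are about right. Neither the direction nor the size of the error can be known without the session distribution.
- **That the many zeros alone defeat the model.** They do not. A Poisson count with mean 0.40 has exp(−0.40) = 67% zeros, the same share as here, and on placebo the zeros are only a bare majority. What matters is the gate together with the pattern of repeat sessions.
- **That a follow-up offset is missing and needed.** An article may leave this to the SAP. It is also debatable, because rescue ends study medication and might affect how long a patient is followed.
- **That negative binomial regression is required.** It handles overdispersion only. If each treated eye has one session it collapses towards Poisson and stays conservative.

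It is also fair to say that the analysis is exploratory. The Statistics section, however, waives adjustment for multiple secondary comparisons; that does not make the interval of a single comparison reliable.

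**Conclusion.** The point holds in a limited form. The named model's own standard errors are not assured for this endpoint. They would be too wide with one session per treated eye (type I error about 1-2%), about right near 1.2 sessions, and too narrow when sessions vary around a mean of two to three (about 12-25%).

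These figures rest on two assumptions. The neovascularisation planning rates stand in for the share of eyes lasered; because rescue need not be laser, that share may be lower. The session distributions are illustrative.

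Severity is minor: the comparison is exploratory, and neither the co-primary tests nor any other confirmatory conclusion is affected.

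**What to change.** Keep the log-linear Poisson model for the number of laser treatments and state that standard errors and confidence intervals use robust (sandwich) variance. Alongside the rate ratio, report by arm the proportion of eyes with any laser and the number of sessions among those treated. The second of these is descriptive, because treated eyes are a subgroup formed after randomisation.

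The cost is one or two sentences in the protocol or SAP, or a check that the full documents already say this. It needs no extra patients or data and leaves the estimated rate ratio unchanged. The article reports that recruitment had not opened, so the change could be made before any outcome data exist.
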